## Abstract

Stroke patients with autonomic dysfunction are more likely to develop cardiac problems, which have been linked to lower functional outcomes and increased mortality. In this study, heart rate variability (HRV) detection paired with the Clinical Feature Scale will be utilized to elucidate the immediate impact of manual acupuncture on autonomic dysfunction of varying severity in the convalescence stroke phase.

This is a randomized, single-blind, controlled clinical trial approach. At a ratio of 1:1, 60 appropriate patients will be randomly randomized into either the experimental or control group. On the basis of symptomatic treatment drugs, the experimental group will additionally undertake acupuncture therapy 3 times a week for 4 weeks, for a total of 12 times. Primary outcomes include 24-hour HRV and 60-minute HRV detection at week 4 compared with baseline. The secondary outcome is the score of clinical feature scale at week 4 compared with the baseline. Adverse events and safety indices will be recorded throughout the experiment. The SPSS V.25.0 statistical program was applied for analysis, and measurement data were expressed as mean ± SD.

## 1. Introduction

Stroke may be followed by central autonomic dysfunction,^[1,2]^ with an early occurrence of from 21.8% to 79%,^[3–5]^ including cardiovascular, endocrine, inflammatory immune, digestive, urinary and other systems.^[6,7]^ The clinical signs include brain-heart syndrome, stress hyperglycemia, shoulder-hand syndrome and sweating problem, and severe instances may lead to sudden cardiac death.^[8]^ Therefore, early detection and treatment of post-stroke autonomic dysfunction cannot be neglected and has major prognostic relevance.

At present, contemporary medical treatment techniques for post-stroke autonomic dysfunction include symptomatic drugs, but difficulties such as no agreement on the dosage,^[9]^ noable side effects^[9–11]^ and complications^[12]^ exist. Therefore, it is vital to investigate a safe, effective, easy, and inexpensive therapy. Acupuncture is commonly employed in traditional Chinese medicine therapies. Studies^[13,14]^ have demonstrated that acupuncture can control the autonomic nerve, and the mechanism of action is mostly represented in the effects of acupuncture on the autonomic nerve at the levels of the cerebral cortex, hypothalamus and pituitary. Heart rate variability (HRV) refers to the small variation between beat-to-beat intervals, which can reflect the relationship between the activity of sympathetic and vagal nerves and the balance and coordination relationship between them. Meanwhile, it can quantitatively reflect the function of autonomic nerve and its effect on cardiovascular regulation.^[9]^ And it is currently the most extensively used indicator to evaluate changes in cardiac autonomic function.^[15]^ Some studies^[16,17]^ found that after acupuncture treatment for stroke patients and patients with autonomic dysfunction secondary to stroke, HRV indexes after treatment were significantly improved compared with those before treatment (*P* < .05). And the degree of improvement was significantly better than the control group (*P* < .05). It is claimed that acupuncture helps treat the autonomic nerve dysfunction induced by stroke.

Therefore, via the objective assessment of HRV detection and clinical feature scale (CFS) ratings, this research further highlighted the immediate impact of manual acupuncture on autonomic nerve dysfunction of varying severity in the convalescence period of stroke. Identify the cumulative impact of the immediate effect and establish that manual acupuncture has various effects on long-term repercussions of severe autonomic dysfunction in the convalescence period of stroke. In order to examine the feasibility and efficacy of acupuncture and moxibustion therapy on autonomic dysfunction in the convalescence period of stroke and to realize its practical value in clinical treatment.

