#### 2.2..1. Inclusion criteria.

Meet the diagnostic criteria of Western medicine:(1) Patients who meet the diagnostic criteria of cerebrovascular disease adopted by the Fourth National Cerebrovascular Disease Academic Conference in 1995, and confirmed by brain CT and MRI;(2) Collect a 24-hour dynamic electrocardiogram from 8 to 9 am on the same day to 8 to 9 am on the next day, and set HRV parameters SDNN < 50ms, SDANN < 40 ms, RMSSD < 15 ms, PNN50 < 0.75%, LF < 300 ms^2^, HF < 200 ms^2^;The first onset is in the 3rd to 6th month;Patients aged 18 to 90 years old;Patients who have signed informed consent.

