## 3. Interventions

### 3.1. Experimental group

All subjects are able to use basic symptomatic treatment drugs, such as hypotensor, lipid-lowering drugs, hypoglycemic drugs, antiplatelet aggregation drugs, etc.

On the basis of symptomatic treatment drugs, acupuncture will be performed. The patients in the acupuncture group will lie in the prone position. The selected acupoints are Neiguan (PC6), Zusanli (ST36). All acupoints are localized according to the WHO Standard Acupuncture Locations^[18]^ and are exhibited in Table 2 and Figure 2. After accurate positioning and routinely disinfecting the local skin of the patient and the hands of the physician with 75% ethanol, physician will insert sterile disposable acupuncture needles (Hanyi, 0.25 mm × 40 mm) into the selected acupuncture points and apply the manipulation of even reinforcing and reducing movement for 1 minute, the rotating angle is between 60° to 210°, and the depth is 0.5 to 1 cun (1 cun ≈ 20 mm). The needles will be kept for 20 minutes after stimulating the acupuncture points to reach De qi (a compositional sensation including soreness, numbness, distention, and heaviness), which is believed to be an essential component for acupuncture efficacy. Acupuncture will be performed once every other day, 3 times a week, for a total of 12 times.

**Table 2 T2:** Locations and manipulations of acupoints.

Acupoint	Location	Manipulation
Neiguan (PC6)	Between the palmaris longus tendon and the flexor carpi radialis tendon, 2 cun above the transverse stria of the distal carpometacarpus	Puncture perpendicularly to a depth of 0.5–1 cun with even reinforcing and reducing movement for 1 min
Zusanli (ST36)	Three cun directly below Dubi, and 1 finger- breadth lateral to the anterior border of the tibia	Puncture perpendicularly to a depth of 1–2 cun with even reinforcing and reducing movement for 1 min

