## 4. Outcomes

### 4.1. Primary outcome

The primary outcome measure is the HRV detection change, comprising 24-hour HRV detection and 60-minutes HRV detection compared with baseline (0 week) at week 4. 24-hour HRV detection comprises SDNN, SDANN, RMSSD, pNN50%, LF and HF. In addition, patients in the experimental group will be detected for 60 minutes at each time of treatment (from 10 minutes before the start of therapy to 30 minutes after the completion of treatment) to identify the change in LF and HF. The SDNN (the standard deviation of all NN intervals) represents the heart rate variability. SDANN (the standard deviation of the averages of NN intervals in all 5 minutes segments of the entire recording) and LF (power in low frequency range) represent the activity of both the sympathetic nervous system and the parasympathetic nervous system. RMSSD (the square root of the mean of the sum of the squares of differences between adjacent NN intervals), pNN50% (NN50 count divided by the total number of all NN intervals) and HF (power in the high frequency range) represent the activity of the parasympathetic nervous system.

During the HRV test, the patient should be in a supine resting posture to avoid tension, excitement, and deep breathing, and the surrounding environment should be kept calm. The test timing must be between 8 AM to 9 AM on the test day.

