### 4.2. Secondary outcomes

The secondary outcome measure is the score change in the Clinical Feature Scale compared with baseline at week 4. With a total score of 0 to 18 points, CFS is used to assess the severity of clinical symptoms of autonomic nerve function. According to heart rate, respiration, blood pressure, body temperature, sweating and posture at the time of seizure, it divides the severity of autonomic nerve dysfunction into 4 grades: normal (0 points), mild (1–6 points), moderate (7–12 points), and severe (≥13 points). All patients will be scored at baseline (week 0) and at the end of treatment (week 4), and the changes in scores before and after treatment will be compared.

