## 5. Discussion

Studies have indicated that post-stroke autonomic dysfunction may remain for at least 6 to 9 months,^[6,19,20]^ rather than being a short-term event. Up to today, most randomized controlled studies have noticed the efficacy of acupuncture on patients with autonomic dysfunction in the acute stage of stroke, but few have found the effectiveness of acupuncture on autonomic dysfunction throughout the convalescent phase after stroke. Therefore, it is worth additional investigation on the effectiveness of acupuncture for improving autonomic dysfunction in the convalescence period of stroke.

Studies have revealed that acupuncture has a bidirectional adjustment to the heart rate of healthy people, which is equivalent to the impact of acupuncture on balancing yin and yang,^[21]^ and the vagus nerve is the key reaction.^[22,23]^ Modern studies^[23–26]^ have found that Neiguan is close to the median nerve and overlaps with the innervated nerve segments of the heart, and the information of acupuncture at Neiguan can reach the cardiovascular center, namely the nucleus of the solitary tract, the posterior hypothalamus and the preoptic area-the front part of the hypothalamus. In the early stage of our research group, a patient with mild autonomic dysfunction in the convalescence period of stroke and a severe patient were acupunctured with bilateral Zusanli and bilateral Neiguan, respectively, and we found that the HRV values of the 2 patients reached equilibrium at 20 minutes and 25 minutes of acupuncture. Based on prior study findings, we anticipated that acupuncture at Neiguan and Zusanli might ameliorate autonomic nerve dysfunction after stroke. Patients exhibied immediate effects with varying durations following acupuncture for 20 minutes, and the initial effects might be cumulative to develop long-term benefits. Studies^[27]^ have shown that acupuncture at Zusanli can activate parasympathetic nerve activity and inhibit sympathetic nerve activity, and Zusanli is an essential acupoint for health care. Its anti-inflammatory effects,^[28]^ antioxidant effects,^[29]^ and effects in enhancing gastrointestinal immunity,^[30]^ regulating intestinal flora and brain-gut peptides,^[31]^ and stabilizing the intestinal micro-ecological environment^[32]^ have been widely proved. Therefore, Neiguan and Zusanli were chosen for this investigation.

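### The aims promise a cumulative and long-term effect, but the last 24-hour HRV and CFS fall in the final treatment week, with no stated gap from needling and nothing measured later

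*Protocol article*

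**What the plan says.** **Aim.** The Introduction sets out to "Identify the cumulative impact of the immediate effect and establish that manual acupuncture has various effects on long-term repercussions of severe autonomic dysfunction". The Discussion repeats the idea as a hypothesis: patients showed "immediate effects with varying durations following acupuncture for 20 minutes", and "the initial effects might be cumulative to develop long-term benefits".

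**Treatment.** Section 3.1: "Acupuncture will be performed once every other day, 3 times a week, for a total of 12 times". Section 3.2 puts clinical observation at one month.

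**Assessments.** Section 4.1 defines the primary outcome as HRV change, "comprising 24-hour HRV detection and 60-minutes HRV detection compared with baseline (0 week) at week 4". Section 4.2 scores the CFS twice, at week 0 and at end of treatment in week 4. In Table 1 the last column is week 4. It sits under the treatment-period heading, carries the intervention mark, and has no follow-up column after it.

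**Timing of HRV.** Section 4.1: "The test timing must be between 8 AM to 9 AM on the test day". The eligibility recording in section 2.2.1 is also set by the clock: "Collect a 24-hour dynamic electrocardiogram from 8 to 9 am on the same day to 8 to 9 am on the next day". Neither section mentions an interval from the last needling.

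**Session recordings.** Section 4.1 also has 60-minute recordings at each session, from 10 minutes before to 30 minutes after treatment, for LF and HF. It describes these for the experimental group only.

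**The concern.** The aim and the schedule do not match. A long-term effect needs at least one measurement after treatment has stopped, and none is planned. This is not detail lost in condensing the protocol into an article, because Table 1 and sections 4.1 and 4.2 state the time points.

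There is a second, weaker problem. The authors expect an immediate response that lasts for a varying time after needling. If the week-4 recording overlaps a session or its after-effect, the experimental arm carries an acute contribution. The control arm has no session and the baseline recording contains no needling, so neither carries one. A between-arm difference at week 4 could then be partly acute yet be reported as cumulative. The same question arises for the CFS, which scores heart rate, respiration, blood pressure, temperature and sweating and has no stated timing relative to a session.

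**Working it through.** **1. Follow-up after treatment.** 12 sessions / 3 per week = 4 weeks. Last assessment = week 4. Scheduled time after treatment = 4 − 4 = 0 weeks.

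**2. Where a week-4 recording can fall.** Assumptions, because the protocol gives neither: week-4 sessions on days 0, 2 and 4 at an hour between 9:00 and 17:00, and recording start at 8:30.

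| Recording starts | Session inside the 24 h? | Gap since last needling |
|---|---|---|
| On a session day | Yes, one | not applicable |
| The morning after a session | No | 15.5 to 23.5 h |
| Two mornings after the last session | No | 39.5 to 47.5 h |

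All three rows satisfy the protocol's wording, so the plan does not settle whether the recording contains a session. If the clock rule in 4.1 is read as covering the session recordings too, sessions fall in the same hour at which 24-hour recordings start and end. A recording begun the morning after one session could then run into the next.

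**3. Size of an acute contribution to LF or HF.** Rise in 24-hour mean power = (ratio − 1) × hours / 24. The documents give neither ratio nor duration, so I assume a ratio of 2 and a range of durations:

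- 50 min (20 min needling plus 30 min after): 0.833 / 24 = 3.5%
- 2 h: 2 / 24 = 8.3%
- 6 h: 6 / 24 = 25%

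The formula applies to mean power only. It does not carry over to SDNN, SDANN, RMSSD or pNN50, which are four of the six 24-hour indices.

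**4. Scale against the planned difference.** Section 4.5 gives a difference of 531.0 and an SD of 593.7 without naming the index. The stated sample size reproduces: 2 × (1.960 + 1.282)² × (593.7 / 531.0)² = 26.3, so 27 per arm, and 27 / 0.9 = 30. Now suppose the index is LF, at its entry ceiling of 300 ms². The rises in step 3 are then about 10, 25 and 75 ms², which is 2%, 5% and 14% of 531.

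As a separate sensitivity check, suppose an arbitrary share of the planned difference were acute. Two-sided t-test power for the remaining sustained part, at 27 per arm, would be:

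| Acute share | Sustained difference | Power |
|---|---|---|
| 0% | 531 | 0.90 |
| 25% | 398.25 | 0.68 |
| 50% | 265.5 | 0.36 |
| 75% | 132.75 | 0.13 |

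The documents give no share, and the LF illustration stays below 25%. The last three rows show sensitivity and are not an estimate.

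**5. What the 60-minute recordings can add.** The change across a session measures the immediate response. The 10-minute pre-needling segments, taken about 48 hours or more after the previous session, could show a trend over 12 sessions. Both are limited to LF and HF in the experimental arm, so any trend is uncontrolled.

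**The case against.** A reader might infer that the week-4 measurements are certainly contaminated, or that the schedule can show neither an immediate nor a cumulative effect. The documents support neither reading. Only week 4, or end of treatment, is fixed. With three sessions a week, four days are session-free, so a clean recording is fully compatible with the plan. The 24-hour clock window in 2.2.1 is an eligibility rule. The rule in 4.1 comes with a supine resting posture, which suits a short test better than a 24-hour recording. The 60-minute recordings do measure the immediate response. All of this stands.

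It can also be argued that long-term describes the consequences of the disorder rather than the durability of acupuncture, that the Abstract speaks of immediate impact, and that the closing paragraphs call this a pilot trial and make no long-term claim. That softens the wording problem but does not remove it. The Discussion expressly links accumulated effects to long-term benefit, and even on the gentler reading an end-of-treatment measurement does not establish an effect on lasting consequences.

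Finally, the acute effect may be small: on the LF illustration even the 6-hour case is 14% of the planned difference. That is fair, and no size is shown for the CFS or the other four indices. An end-of-treatment endpoint is also legitimate in itself. The objection is to the aim attached to it and to the missing interval.

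**Conclusion.** The firm part needs no assumption. With no assessment after week 4 of a four-week treatment, the trial cannot support a long-term or durability conclusion, whatever the gap from needling.

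The second part is conditional. Because no interval from the last session is stated, a one-arm acute effect in the week-4 24-hour HRV or CFS cannot be excluded, but it is not certain. Its size is not in the documents. The range of 3.5% to 25% for LF or HF power rests on an assumed doubling lasting 50 minutes to 6 hours.

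The session recordings document the immediate response, and possibly a trend, in one arm only. They do not provide a randomised estimate of a cumulative effect. The sample size calculation is not affected by this point.

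**What to change.** - In the Introduction, restate the aim as the effect at end of treatment (week 4) and drop the long-term claim. Keep the Discussion and the eventual conclusions to the same scope.
- In Table 1 and sections 4.1 and 4.2, take the final 24-hour HRV and CFS on a session-free day at a fixed interval after the 12th session (for example, recording start at least 24 hours later). Assess controls on the same study day.
- Describe any trend in the pre-needling segments as an uncontrolled, experimental-arm observation.

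If a long-term claim is to stay, it needs an assessment after treatment in both arms, which is a larger change.

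The cost of the main fix is tighter scheduling, possibly one additional attendance (the protocol does not say whether patients are inpatients), and a narrower claim. The number of 24-hour recordings and the acupuncture schedule do not change.

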## 2. Methods

### 2.1. Study design

This randomized, single-blind, controlled clinical trial will be conducted in Longhua Hospital Affiliated to Shanghai University of Traditional Chinese Medicine. A flow diagram of the trial is shown in Figure 1. The schedule of enrollment, interventions and assessments are presented in Table 1.

**Table 1 T1:** The schedule of enrollment, interventions and assessments are presented.

	Sutdy Period					
	Screening	Baseline	Treatment Period (wk)			
Timepoint		*0*	*1*	*2*	*3*	*4*
Enrolment						
Eligibility screen	X					
Informed consent	X					
Allocation		X				
Interventions:						
*Experimental group*			X	X	X	X
*Control group*			X	X	X	X
Assessments:						
*Physical examination*		X				
*Acupuncture Safety and tolerance test*		X				
*Blind method success rate test*		X				
*24-h HRV*		X				X
*60-min HRV*			X	X	X	X
*CFS*		X				X
*Concomitant medication*		X	X	X	X	X
*Adverse reaction record*		X	X	X	X	X

CFS = clinical feature scale, HRV = heart rate variability.

Physical examination include height, weight, blood pressure and heart rate.

**Figure 1. F1:**
[figure not shown]
Flow diagram. HRV = heart rate variability.

### 2.2. Patient recruitment

This study intends to enroll 60 patients who match the diagnostic criteria started in November 2021, all from Longhua Hospital Shanghai University of Traditional Chinese Medicine. The researcher took the initiative to present the study, and the participants volunteered to engage in it. After the doctor completed screening according to the inclusion and exclusion criteria, the participants might be included if they satisfied the requirements. Before randomization, all patients are asked to submit written informed permission.

#### 2.2..1. Inclusion criteria.

Meet the diagnostic criteria of Western medicine:(1) Patients who meet the diagnostic criteria of cerebrovascular disease adopted by the Fourth National Cerebrovascular Disease Academic Conference in 1995, and confirmed by brain CT and MRI;(2) Collect a 24-hour dynamic electrocardiogram from 8 to 9 am on the same day to 8 to 9 am on the next day, and set HRV parameters SDNN < 50ms, SDANN < 40 ms, RMSSD < 15 ms, PNN50 < 0.75%, LF < 300 ms^2^, HF < 200 ms^2^;The first onset is in the 3rd to 6th month;Patients aged 18 to 90 years old;Patients who have signed informed consent.

#### 2.2..2. Exclusion criteria.

Pregnant or lactating women;Patients with serious cardiac arrhythmia, myocardial infarction, coronary heart disease, infection, tumor and other serious conditions;Combined with severe liver, kidney, lung, blood and other systemic diseases.

### 2.3. Randomisation and allocation concealment

The subjects will be randomly allocated to an experimental group or control group at a ratio of 1:1 by the random number generated by SPSS V.25.0. The trial was primarily blinded to assess data collectors, data analysts, and outcome judges, and to conceal assessment results and trial results from all investigators, staff, and subjects. The treatment plan adopted by the physician for the subjects should be consistent with the treatment plan corresponding to their random number.

## 3. Interventions

### 3.1. Experimental group

All subjects are able to use basic symptomatic treatment drugs, such as hypotensor, lipid-lowering drugs, hypoglycemic drugs, antiplatelet aggregation drugs, etc.

On the basis of symptomatic treatment drugs, acupuncture will be performed. The patients in the acupuncture group will lie in the prone position. The selected acupoints are Neiguan (PC6), Zusanli (ST36). All acupoints are localized according to the WHO Standard Acupuncture Locations^[18]^ and are exhibited in Table 2 and Figure 2. After accurate positioning and routinely disinfecting the local skin of the patient and the hands of the physician with 75% ethanol, physician will insert sterile disposable acupuncture needles (Hanyi, 0.25 mm × 40 mm) into the selected acupuncture points and apply the manipulation of even reinforcing and reducing movement for 1 minute, the rotating angle is between 60° to 210°, and the depth is 0.5 to 1 cun (1 cun ≈ 20 mm). The needles will be kept for 20 minutes after stimulating the acupuncture points to reach De qi (a compositional sensation including soreness, numbness, distention, and heaviness), which is believed to be an essential component for acupuncture efficacy. Acupuncture will be performed once every other day, 3 times a week, for a total of 12 times.

**Table 2 T2:** Locations and manipulations of acupoints.

Acupoint	Location	Manipulation
Neiguan (PC6)	Between the palmaris longus tendon and the flexor carpi radialis tendon, 2 cun above the transverse stria of the distal carpometacarpus	Puncture perpendicularly to a depth of 0.5–1 cun with even reinforcing and reducing movement for 1 min
Zusanli (ST36)	Three cun directly below Dubi, and 1 finger- breadth lateral to the anterior border of the tibia	Puncture perpendicularly to a depth of 1–2 cun with even reinforcing and reducing movement for 1 min

